### Oversight and monitoring

The sponsor in collaboration with the Steering Committee decided not to establish a formal Data Monitoring Committee for this trial considering the following 5 points:
This trial aims to evaluate the uselessness of prophylactic drain placement after gastrectomy, a clinical practice that is still widely used but that has been already been discouraged by international guidelinesEvidence in literature does not suggest a highly favorable or unfavorable result. The design of a non-inferiority trial was deemed necessary due to the small estimated difference between the two groups on the outcome considered for this studyThe inclusion criteria and the study design (leaving the decision on the POD of drain removal to each participating center according to their usual clinical practice) consistently reduce the (already limited) risksAllowing any type of drain in the study protocol (leaving the decision to each center according to their usual clinical practice) does not define this study as a device studyPatient population is above 18 years old

All the participating centers are part of GIRCG quality of surgery and postoperative care was considered adequate for this trial according to our previous studies [25, 26].

The wide inclusion criteria and the balancing between type of resection aim to result in a trial as close as possible to the everyday Western clinical practice.

Considering that both arms include treatment commonly applied in daily clinical practice (drain placement and drain avoidance) under the inclusion criteria considered in this trial, the IRBs (of each participating center), in accordance with the legal service of all the participating center, agreed to ensure ADiGe Trial using the hospital insurance of each center. Therefore, in case of claims for damages, the responsible would be the insurance coverage of assistance activities of the center that recruited and treated the patient.

#### Safety and adverse event monitoring

Any untoward medical occurrence in a patient without regard to the possibility of a causal relationship has been defined as an adverse event (AE). Investigators from each participating center will record any AE from the day of operation until the end of the observation period. All AEs will be documented in the patient’s medical record and AE form including any workup or treatment needed and grading (according to the Common Terminology Criteria for Adverse Events), according to everyday clinical practice.

AE, expected to be related with the study treatment (bleeding from drain site, skin infection around the drain site and pain), will be also recorded in the study CRF. Any unexpected AE, considered by the investigator as causally related with the treatment, will be recorded in the study CRF and reported to the steering committee for safety reporting purposes.

AE that meets the following criteria will be recorded as serious adverse event (SAE): life-threatening condition (immediate risk of death), severe or permanent disability, and prolonged hospitalization. All SAE will be recorded in the study CRF. Moreover, the investigators will report to the local IRB and the steering committee, as soon as possible, but in no event later than 2 working days, any SAE that is deemed by the local investigator to be probably or definitely related to the study treatment. The steering committee will then review the report and send it to the promoting center’s IRB within 2 working days. SAEs, occurring after a patient is discontinued from the study, will not be reported unless the investigators will determine that they are related to the study treatment. If the number of SAE is higher than reported in the recently published Gastrodata study on complications after gastrectomy [27], patient enrollment will be terminated immediately, and the steering committee will reassess the safety of the trial.

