## Introduction

### Background and rationale

Prophylactic drain placement after gastrectomy has been advocated until the last few years as the main tool for early diagnosis and treatment of surgical intra-abdominal complications, especially with regard to anastomotic or duodenal stump leakages. Evidence against routine drain use after colorectal resection [1, 2] raised the interest on this argument. There was also interest for upper gastrointestinal surgery and, in 2015, a Cochrane meta-analysis [3] on 4 RCTs concluded that there was no convincing evidence to the prophylactic drain placement after gastrectomy. Nevertheless, the authors evidenced the moderate/low methodological quality of the included studies and highlighted how 3 studies out of 4 came from Eastern countries [3]. Moreover, randomization was never mentioned in 1 of the 4 articles, classified as RCTs. After 2015, other retrospective studies have been published, but most of them included a small number of patients and heterogeneous types of surgery, including multi-visceral and R2 resection [4–7]. Our study group recently published an updated meta-analysis including both RCTs and cohort studies, comparing the use of prophylactic drain with drain avoidance [8]. The results suggest that skipping drainage can reduce morbidity and length of stay, without affecting other major surgical outcomes. However, as for the Cochrane meta-analysis, the strength of this evidence is blunted by the limited quantity and quality of data available. Waiting for further evidence, the use of prophylactic abdominal drain after gastrectomy is currently left up to the surgeon’s preference.

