#### Postoperative procedure

All patients follow the usual postoperative pathway of each participating center except for abdominal drain management. Prophylactic drain in group A patients is daily evaluated checking for suspicious debt. In patients with a normal debt, a methylene blue test (the patient is asked to drink 200 ml of water/tea with 5 ml of methylene blue) is performed on postoperative day (POD) 4 and the test is considered negative if no blue staining of drain output is apparent within 60 min (the 200-ml colored solution stays in the esophageal/gastric lumen and this is considered as an indirect sign of the absence of an anastomotic leak). After the blue test is confirmed as negative, the drain can be removed. Each center is allowed to remove drain on whatever POD after a negative test. Drain management in patients with a suspicious debt or positive blue test is left to center preference (no further blue tests are planned). Postoperative complications are recorded until POD 30 or in hospital if hospital stay is longer than 30 days.

Reoperation under general anesthesia and/or percutaneous abdominal/thoracic drain placement during the first 30 PODs for any cause related to the previous gastrectomy is considered as an event in both groups. The cause-effect relationship decision is left to the lead site surgeon and in case of doubt, the investigator can ask for support from the steering committee. This specification was considered mainly necessary in case of unrelated pathology acquired after discharge but within POD 30 (e.g., operation for road accident). After discharge, patients are evaluated in the outpatient clinic on POD 30 or in the subsequent week. Follow-up calls are conducted by authorized medical or nursing staff at POD 60 ± 7 and 90 (max + 7 days) in order to assess patient’s clinical status.

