### Outcomes

The primary composite endpoint is the cumulative incidence of reoperation and/or percutaneous drainage placement by the 30th postoperative day.

Secondary endpoints are as follows:
Incidence, severity, and time to diagnosis of anastomotic and duodenal leakLength of hospital stayOverall 30 days morbidity or in hospital if longer than 30 daysOverall 90 days mortality30 days readmission rate

Length of hospital stay is considered from the day of operation until discharge at home or at other facilities, or death. Postoperative complications, including anastomotic and duodenal leak, are classified according to the International Consensus on a Complications List After Gastrectomy for Cancer [23] and stratified by severity using the Clavien-Dindo classification [24].

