## Discussion

Prophylactic drain in gastrectomy is still widely applied, even if some evidence against its routine use has been reported in four RCTs [13–15, 28]. Nevertheless, as highlighted in Cochrane meta-analysis, these studies lack in methodological quality and mainly come from Eastern countries [3].

So far, the only Western RCT has been published in 2005 by Alvarez and included 60 patients that underwent total gastrectomy [13]. The author reported a significantly longer hospital stay (18.8 vs 12.9 days) and higher morbidity rate (37.9% vs 9.7%) in the drain group. Reoperation rate was rather high in both groups, with a trend in favor of no drain population (9.7% vs 24.1%). However, the results of this study are jeopardized by the small sample size, unclear primary outcome, and inclusion of multivisceral resection.

The largest Eastern RCT has been published by Jiang and included a total of 170 patients treated with total or subtotal gastrectomies aimed to compare complication rate between the drain and no drain groups [14]. The trial resulted in a comparable morbidity rate with a total of three patients with intra-abdominal abscess (one in the drain, two in the no drain group) that required ultrasound-guided percutaneous drainage.

A multi-institutional analysis from US on 344 patients that underwent total gastrectomy observed no differences in overall complication rate and 30 day mortality. Need for secondary drain placement (10% vs 9%) or reoperation (13% vs 8%) were also comparable [6].

Based on these limited evidence, we designed the ADiGe Trial aiming to contribute to a critical re-evaluation of the role of prophylactic drain placement in gastrectomy. Of note, the ADiGe Trial is the first RCT studying the use of prophylactic drain in gastrectomy in a large cohort of Western patients.

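### The SAE list names prolonged hospitalization but not readmission, so a primary event treated after discharge need not count towards the SAE-based enrolment-termination rule

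*Protocol article*

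**What the plan says.** All references are to the protocol article.

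- **SAE definition** (Safety and adverse event monitoring). The criteria are "life-threatening condition (immediate risk of death), severe or permanent disability, and prolonged hospitalization". Nothing marks the list as illustrative. New hospitalization and readmission do not appear. Death is not listed either, but that is a separate matter.
- **Use of the SAE count** (same section). Enrolment is terminated at once under this condition: "If the number of SAE is higher than reported in the recently published Gastrodata study on complications after gastrectomy". SAEs judged probably or definitely related to study treatment must reach the local IRB and the steering committee within 2 working days.
- **Primary event** (Outcomes). "The primary composite endpoint is the cumulative incidence of reoperation and/or percutaneous drainage placement by the 30th postoperative day". Postoperative procedure spells this out as "Reoperation under general anesthesia and/or percutaneous abdominal/thoracic drain placement during the first 30 PODs for any cause related to the previous gastrectomy". Its explanation of the relatedness condition refers expressly to the time after discharge but before POD 30.
- **Capture after discharge.** Postoperative procedure: "After discharge, patients are evaluated in the outpatient clinic on POD 30 or in the subsequent week". The 30-day readmission rate is a secondary endpoint (Outcomes).
- **Oversight** (Oversight and monitoring). The sponsor and steering committee decided against a formal Data Monitoring Committee.

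**The concern.** The trial asks whether leaving out the drain leads to more reoperations and percutaneous drainages. Some of these will happen after the patient has gone home, and the article plans for that by following patients to POD 30 and counting readmissions. The SAE list does not follow suit. It recognises a longer stay but not a new one, so whether the same complication is serious turns on whether the patient had already been discharged.

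Two safety mechanisms depend on this classification. The termination rule works on the number of SAEs, so events that escape the definition make it fire later or not at all. The 2-working-day route to the IRB applies only to SAEs, so a treatment-related readmission for drainage can fall outside it. Without a Data Monitoring Committee, both carry more weight than they otherwise would.

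**Working it through.** The point concerns a definition, so the main check sets the passages side by side. The arithmetic only bounds the size.

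**Step 1. One event, two settings.** Take a collection drained percutaneously on POD 14, with no immediate risk of death and no disability.

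| | Still in hospital, stay extended | Discharged on POD 10, readmitted on POD 14 |
|---|---|---|
| Primary event | yes | yes |
| 30-day readmission endpoint | no | yes |
| Recorded as an AE | yes | yes |
| Life-threatening | no | no |
| Severe or permanent disability | no | no |
| Prolonged hospitalization | yes | not as written |
| **SAE** | **yes** | **need not be** |

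Only the date of discharge differs. The gap lies in new hospitalization. A re-intervention during the index stay will usually qualify already, because it prolongs the stay or answers a threat to life.

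**Step 2. The article's own figures** (Sample size).

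- Drain: 7/115 + (1 − 0.70) × 1/86 = 6.44%. Reproduced.
- No drain: 3/115 + (1 − 0.35) × 2/84 = 4.16%. Reproduced.
- The stated 182 per arm also reproduces, with power 80.1% at one-sided 5% and a margin of 3.56 points. Nothing in this point changes it.

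**Step 3. Expected primary events at 182 per arm.**

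- Drain: 182 × 0.0644 = 11.7
- No drain: 182 × 0.0416 = 7.6
- Total: 19.3

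These are all expected primary events, not those that escape the SAE list.

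**Step 4. Events missed, for an assumed escaping share f.** The article gives no share of events arising after discharge, so each f is an assumption. Missed = expected events × f.

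| f, drain | f, no drain | Missed, drain | Missed, no drain |
|---|---|---|---|
| 10% | 10% | 1.2 | 0.8 |
| 30% | 30% | 3.5 | 2.3 |
| 50% | 50% | 5.9 | 3.8 |
| 10% | 30% | 1.2 | 2.3 |
| 20% | 40% | 2.3 | 3.0 |
| 30% | 10% | 3.5 | 0.8 |

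With equal shares of 10%, 30% and 50%, the totals are 19.3 × f = 1.9, 5.8 and 9.6. Readmissions for complications that are not primary events can escape too, but the article gives no rate from which to count them.

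**Step 5. Direction between arms.** At the planned rates the no-drain arm loses more SAEs in absolute number only if f(no drain) × 4.16 > f(drain) × 6.44, that is, if its escaping share exceeds 6.44/4.16 = 1.55 times that of the drain arm. At the 10% no-drain rate of the null hypothesis, the threshold falls to 6.44/10 = 0.64. In relative terms, the arm with the larger escaping share is under-counted more. The document fixes none of these shares.

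**The case against.** **The event is not lost.** This stands. A readmitted patient counts in the primary endpoint, in 30-day readmission and as an AE: "Investigators from each participating center will record any AE from the day of operation until the end of the observation period". Complications are also graded by Clavien-Dindo. None of these depends on the SAE list, so the primary non-inferiority analysis and the planned arm comparisons are untouched.

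**SAEs are not the only ongoing safety signal.** This stands as well. Any unexpected AE that the investigator considers causally related goes to the steering committee whatever its seriousness, and regular audits with the centers are planned. However, no time limit is stated for that AE report, and the termination rule does not use it.

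**A site may take prolonged hospitalization to include readmission, and the full protocol may say so.** Possible, but the printed definition does not. Nine centers could read it differently, which is itself a reason to settle the wording.

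**A stronger reading is tempting.** A reader might infer that the shorter-stay, no-drain arm is under-counted, so that leaving out the drain is made to look safe. The article does say of its group's meta-analysis: "The results suggest that skipping drainage can reduce morbidity and length of stay". Its Discussion gives mean stays of 18.8 v 12.9 days (drain v no drain) in the one Western RCT. This does not carry the inference, for three reasons.

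- The article gives no post-discharge event share by arm, and Step 5 shows that the direction depends on it.
- The stay figures come from a 60-patient trial that the article itself regards as compromised. Its drain arm also had more morbidity (37.9% v 9.7%) and more reoperation (24.1% v 9.7%), so its longer mean stay may reflect complicated patients rather than a generally later discharge.
- The article describes no comparison of SAEs by arm. The termination rule sets a number of SAEs against an external study and mentions no split.

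**Conclusion.** The concern holds as a defect in a stated rule, not as a demonstrated bias. Read as printed, the SAE definition leaves out primary events treated on readmission in either arm, so the count is too low and depends on discharge timing. What suffers is the termination rule and the expedited reporting of related SAEs.

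The number affected cannot be derived from the document. On assumed escaping shares of 10% to 50%, equal in both arms, it would be about 2 to 10 of some 19 expected primary events. This rests on the planned rates, 182 patients per arm, and sites applying the list literally. A difference between arms is possible if length of stay differs, but the document does not show one. How close the trial would come to the termination threshold cannot be said, because neither the benchmark figure nor its counting definition is in the article.

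**What to change.** Change the third criterion to *requires or prolongs hospitalization (including readmission)*, in the protocol and in the CRF guidance, and apply it to both arms.

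Before doing so, check how the external Gastrodata figure used in the termination rule was counted, and put both counts on the same definition. If the benchmark leaves out readmissions, widening only the trial's count could trigger the rule artificially. If it includes them, the present count understates the trial's position.

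The cost is one sentence, a few more SAE forms and a somewhat higher SAE total. Readmissions and re-interventions are already collected as endpoints. Classing every reoperation or percutaneous drainage as an SAE is not needed, since the gap is new hospitalization.

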### Sample size

According to a systematic review published in May 2020 [8], the cumulative incidence of reoperation in two RCTs was 7/115 = 6.1% (95% CI 2.5–12.1%) in the drain group and 3/115 = 2.6% (95% CI 0.5–7.4%) in the no drain group. Cumulative incidence of additional drain was 1/86 = 1.2% (95% CI 0.03–6.3%) in the drainage group and 2/84 = 2.4% (95% CI 0.3–8.3%) in the no drain group. Assuming a 70% of overlap between the two procedures in the drain group, the estimated proportion of the composite outcome is 6.44%, while assuming a 35% overlap in the no drain group, the estimated proportion of the composite outcome is 4.16%.

Hence, we assumed a reference group proportion of 6.44%, and a treated group proportion of 10% under the null hypothesis of inferiority and 4.16% under the alternative hypothesis of non-inferiority. A sample size of 182 in each group, corresponding to 364 patients overall, achieves 80% power to detect a non-inferiority margin difference between the group proportions of 3.56% (= 10–6.44%), with a one-sided significance level of 5%. A power curve for treated group proportion ranging from 3 to 7% under the alternative hypothesis of non-inferiority is presented in Fig. 3.

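### The SAE rule that ends enrolment compares an undefined number with another study's figure, ignores arm and chance, and counts events under criteria that do not list death

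*Protocol article*

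**What the plan says.** All of this is in the protocol article.

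- **Trigger** (Safety and adverse event monitoring): "If the number of SAE is higher than reported in the recently published Gastrodata study on complications after gastrectomy". The external figure is cited but not given.
- **Consequence** (same section): "patient enrollment will be terminated immediately, and the steering committee will reassess the safety of the trial".
- **SAE definition** (same section): "life-threatening condition (immediate risk of death), severe or permanent disability, and prolonged hospitalization". Death is not one of the three criteria.
- **What is collected** (same section): "All SAE will be recorded in the study CRF". Only SAEs judged probably or definitely related to study treatment go to the local IRB and the steering committee, within 2 working days. The trigger does not say which of the two sets it counts.
- **Oversight** (Oversight and monitoring): the sponsor and steering committee "decided not to establish a formal Data Monitoring Committee". The SAE comparison is therefore the only halting rule that the article states.
- **Mortality** (Outcomes): 90-day mortality is a secondary endpoint. Nothing links it to the halting rule.

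**The concern.** A compulsory, immediate halt needs a trigger that two people would calculate in the same way. This one can be read as a count of events, a count of patients or a rate, over all SAEs or only related ones, at any time. As a raw count it compares two studies of possibly very different size. As a rate it acts on the point estimate, so ordinary sampling variation is enough to end enrolment.

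The trial asks whether omitting the drain causes harm, yet the rule names no arm. The natural reading is a pooled total, which responds to the average over both arms and not to the contrast that the trial was set up to study. A death enters the total only if it also meets one of the three listed criteria.

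Recruitment could thus be interrupted by chance, or a safety signal in the no-drain arm could pass unnoticed by the one rule meant to catch it.

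**Working it through.** **Inputs.** The rule carries no number to reproduce. The only plan figure needed is the horizon of 404 patients (Sample size). It reproduces: the unpooled formula gives n = (1.645 + 0.842)² × (0.0644×0.9356 + 0.0416×0.9584) / 0.0584² = 181.5, so 182 per group and 364 in total, and 364/0.9 = 404.4. The benchmark SAE rate r, the reference cohort size M and the look schedules are not in the documents. They are assumptions, shown as ranges. An SAE is treated as one yes/no outcome per patient.

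**1. Literal count.** The rule fires if X > M×r, with X ~ Binomial(404, true rate). For example, with r = 10% and equal safety, X has mean 40.4 and SD √(404×0.1×0.9) = 6.03. With M = 300 the threshold is 30, and P(X ≥ 31) = 0.954. With M = 600 the threshold is 60, and P(X ≥ 61) = 0.0008.

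| Reference cohort M | Fires at equal safety, r = 10–30% |
|---|---|
| 200–300 | 95–100% |
| 404 | 48–51% |
| 500 | 0.1–5% |
| 600 or more | under 0.1% |

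With M = 1,000 and a doubled SAE rate (r = 10%, true 20%), X has mean 80.8 and SD 8.04, and P(X ≥ 101) = 0.008. At r = 20% or 30% it is smaller still.

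**2. Rate, no allowance for chance.** The rule fires if the running pooled proportion exceeds r at any look. One look is exact binomial; repeated looks are simulated (40,000 trials per setting, r = 10, 15, 20 and 25%).

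| Looks | True rate = r | True rate = 0.8r |
|---|---|---|
| One, at 404 | 47–51% | 1–7% |
| Four (101, 202, 303, 404) | 68–71% | 12–26% |
| After every patient | 93–96% | 75–78% |

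**3. Sensitivity to a difference between arms.** Put the drain arm at r/2 and the no-drain arm at r, a doubling between arms, with 202 per arm. For r = 20% the pooled count has mean 202×0.10 + 202×0.20 = 60.6 and SD √(18.18 + 32.32) = 7.11, against a threshold of 80.8. The exact probability of exceeding it at 404 is 0.003. It is 0.030 for r = 10% and below 0.001 for r = 30%.

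A milder case shows the same thing in another way. With the benchmark at 20%, compare 14% (drain) and 24% (no drain) with 19% in both arms. The pooled check fires in 31% and 31% at one look, 55% and 56% with four looks, and 91% and 91% after every patient. It fires equally often whether or not the arms differ.

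**4. Illustrative replacement.** Take looks after 100, 200 and 300 patients. Pause if the lower limit of a two-sided 95% interval for the pooled proportion exceeds r, or if the lower one-sided 99% limit for no drain minus drain exceeds zero. With both arms at r (10–25%), a pause occurs at some look in about 5–7% of trials using Wald or exact limits for the pooled proportion. Wilson limits give 8–9%. With both arms at 30% against r = 20% it pauses in 98%. In the doubling scenario of step 3 it pauses in about 30%, 60% and 83% for r = 10, 20 and 30%.

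**The case against.** **The false-halt figures depend on assumptions.** The highest ones need a check after every patient and a true rate equal to the benchmark, and the article states neither. A reader might infer that the rule would probably halt a safe trial. The documents do not support that as a general statement: with a true rate 20% below the benchmark, four looks halt 12–26% and one look 1–7%. On the count reading, a reference cohort near the trial's own size would behave less extremely. This objection stands and limits the claim.

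**The benchmark is unseen.** Its design, case mix, size and SAE figure are not in the documents, so no argument that its population does not match this one can be made here. This stands too.

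**Harm in one arm is not invisible to the rule.** A reader might infer that a pooled rule never fires when only the no-drain arm is worse. That is wrong: at 14% and 24% against 20% it fires in 31% at one look and in 55% with four. It does so through chance in the pooled rate, as step 3 shows, so the insensitivity remains.

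**Other safeguards exist.** Related SAEs reach the IRB and steering committee within 2 working days, and the postoperative course is unblinded, so reports can be attributed to an arm. Deaths are collected as 90-day mortality and compared by arm, and many would be preceded by a life-threatening event that already counts. It would be too strong to say that deaths are lost. The halt also leads to a reassessment, not to a finding of harm. All of this lowers the severity, but none of it makes the trigger computable.

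**An article condenses the protocol.** A look schedule or table layout could sit in the full document. But the article itself states the trigger as a number and lists the SAE criteria, and it fixes both badly.

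**Conclusion.** The concern holds in a limited form. The only stated halting rule cannot be applied consistently, and under either reading it separates a safe trial from a harmful one poorly. As a count, its behaviour is set mainly by the size of another study. As a rate, a trial exactly as safe as the benchmark halts with probability from about 0.5 (one look) to 0.93–0.96 (every patient), and less often if the trial is safer. Because it names no arm, a doubling of the SAE rate between arms can leave a pooled check at 404 firing in about 3% of trials or fewer. A death counts only if it also meets a listed criterion.

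The sizes rest on assumed benchmark rates, cohort sizes and look schedules, on one yes/no SAE outcome per patient, and on reading the total as pooled, which is natural but not stated. The margin, sample size and primary analysis are unaffected. This should be fixed; it is not a fatal flaw.

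**What to change.** Amend the safety section in two places.

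1. List death as an SAE criterion, so that the definition agrees with the mortality endpoint.
2. Replace the number of SAEs with the proportion of patients with at least one SAE, overall and by arm. State whether all or only related SAEs count, give the benchmark proportion taken from the cited study, and name a few fixed looks. Enrolment would pause for steering-committee review only when a confidence limit, not the point estimate, crosses the benchmark or, for the difference between arms, zero.

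The looks and limits in step 4 of the working are an illustration with a false-pause probability of about 5–7%. The trial team should set its own thresholds and report their operating characteristics.

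The cost is one amendment and a short tabulation of CRF data at each look. The price is a slightly slower trigger, since a confidence limit crosses later than a point estimate. The existing 2-working-day reporting of related SAEs would continue in the meantime.
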